**Primary outcomes**		
msSBP/msDBP	Three consecutive sitting BP measurements will be performed at 3-min intervals, and the average of three measurements will be used as a reference for each patient’s msSBP and msDBP.	0, 3, 14, 21, 28
**Secondary outcomes**		
BP control rate	Defined as msSBP/msDBP < 140/90 mmHg	28
TCM syndrome scoring	TCM syndrome scoring scale will be used for evaluating the improvement of symptoms (Additional file 3).	0,28
**Biochemical index**		
Blood lipids	On days 0 and 28 of the treatment cycle, the researchers will collect the morning fasting blood of each subject for biochemical detection.	0,28
Blood sugar		
Urine microalbumin		
Uric acid		
Homocysteine		
C-reactive protein		

#### BP measurement

We will use a proven medical electronic sphygmomanometer equipped with an upper arm. During the first visit, BP should be measured in both upper arms; the side with a higher reading will be selected as the upper arm for further study. Three consecutive sitting BP measurements will be performed at 3-min intervals, and the average of three measurements will be used as a reference for each patient’s clinical BP. While measuring BP, pulse rate will be measured.

#### Participant timeline {13}

The content and key points of data collection in the experiment are as follows:
Screening period (− 14 to 0 days): inclusion evaluation will be conducted in the first 14 days.Intervention period (28 ± 2 days): telephone follow-up will be conducted on the 3rd day and 3rd week; field follow-up tests at the study center will be performed at weeks 2 and 4.

Different items will be measured according to the point in time when the data are collected. The details are shown in Fig. 2.

**Fig. 2 Fig2:**
[figure not shown]
Schedule of enrollment, interventions, and assessments

#### Sample size {14}

The trial will check for superiority between the treatment group (treatment with Val/Aml and TJT) and the control group (treatment with Val/Aml and TJT placebo).

The calculation of sample size is based on the hypothesis of superiority and the method of comparing the two means. Assuming that the class I error rate is *α* = 0.05 and the class II error rate is *β* = 0.2, and based on a previous study [19], the test group DBP after treatment (*πc*) can be set as follows: DBP, 8.3 ± 5.53 mmHg, and the control group DBP after treatment (*πt*) can be set as follows: DBP, 6.3 ± 4.31 mmHg based on the effectiveness test sample size calculation formula:
$$ N=\left[2{\left({Z}_{1-\alpha }+{Z}_{1-\beta}\right)}^2{\delta}^2\right]/{\left({\pi}_T-{\pi}_c\right)}^2 $$

**δ**^2^ = (S1^2^ + S2^2^)/2; S1 and S2 are the standard deviations of the control group and treatment group, respectively; *α* = 0.05, *Z*_1−*α*_ = 1.96, *β* = 0.1, *Z*_1-*β*_ = 1.28, (*Z*_1 − *α*_ + *Z*_1 − *β*_)^2^ = 6.2. Then, each group needs a sample size of 120. The quality of the study will be strictly controlled during the trial. After considering the Good Clinical Practice (GCP) shedding rate (20%) and expanding the number of samples, we decided to recruit 288 patients in this trial, including 144 patients in the treatment group and 144 patients in the control group. The total number of cases in the two combinations will be 288: 144 in the treatment group and 144 in the control group.

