#### Principles and methods of statistical analysis

All analyses will be conducted with SPSS version 26.0 (IBM SPSS Inc., Armonk, NY, USA) or SAS version 9.4 (SAS Institute, Inc., Cary, NC, USA). The data analysis, data entry, and data management of each research center will be conducted in the Evidence-based Medicine Research Center of Shandong University of Traditional Chinese Medicine. Bilateral tests will be used for all statistical tests, with *P* < 0.05 being considered statistically significant (unless otherwise specified). The 95% confidence interval will be calculated. The quantitative index will include the calculation of the mean, standard deviation, median, minimum, and maximum. The classification index is described by the number of cases and percentages of each category. The two study groups will be compared using an independent two-sample Student’s *t* test. For categorical variables, a *χ*^2^ test will be used when appropriate. A Wilcoxon paired signed-rank test will be used for within-group comparisons.

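### The sample-size section contradicts itself on error rates, and its stated formula and variance do not give 120 per group; 20% loss from 144 leaves about 115, with power above 80% but below 90%

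*Protocol article*

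**What the plan says.** All the planning figures are in the protocol article, Sample size {14}. The section opens with "Assuming that the class I error rate is *α* = 0.05 and the class II error rate is *β* = 0.2", which is 80% power. It takes the test-group value as "DBP, 8.3 ± 5.53 mmHg" and the control-group value as 6.3 ± 4.31 mmHg, and describes both as DBP after treatment. Its formula is N = 2(Z for alpha + Z for beta)² × δ² / (difference)², where δ² is the average of the two squared SDs.

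The list of inputs under the formula then gives 1.96 for alpha and "β* = 0.1, *Z*_1-*β*_ = 1.28", which is 90% power, followed by "Z*_1 − *α*_ + *Z*_1 − *β*_)^2^ = 6.2". The result is "Then, each group needs a sample size of 120". The step to 144 per arm and 288 in total is introduced with "After considering the Good Clinical Practice (GCP) shedding rate (20%) and expanding the number of samples".

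Principles and methods of statistical analysis adds "Bilateral tests will be used for all statistical tests", with significance at P < 0.05.

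**The concern.** The section prints its inputs, formula, intermediate value and result, so the calculation can be followed from start to finish, and it does not hold together. Two different type II error rates are stated. The squared sum does not match the z values printed beside it. The value 6.2 fits a one-sided 5% test with 80% power, whereas the analysis is two-sided. The loss allowance also does not protect the 120 said to be needed.

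At stake is which power the trial was designed for. A non-significant msDBP result would be read against 80% by one reader and 90% by another, and neither could trace the sample size to the power they assumed.

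**Working it through.** **Inputs, all from Sample size {14} unless noted.** Expected values 8.3 (SD 5.53) and 6.3 (SD 4.31) mmHg; difference 8.3 − 6.3 = 2.0 mmHg; 1:1 allocation; 20% loss; two-sided tests at 0.05 (Principles and methods of statistical analysis).

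**Variance by the stated rule.** δ² = (5.53² + 4.31²)/2 = (30.58 + 18.58)/2 = 24.58, so SD = 4.958.

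**Squared sum.** (1.96 + 1.28)² = 3.24² = 10.50, not 6.2. For one-sided 5% and 80% power the value is 6.18, which rounds to 6.2.

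**Trying to reproduce 120.** With K the squared sum, N = 2 × K × 24.58 / 2.0² = 12.29 × K:

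| Setting | K | N per group |
|---|---|---|
| Printed factor 6.2 (one-sided 5%, 80%) | 6.2 | 76.2 |
| Two-sided 5%, 80% | 7.85 | 96.5, so 97 |
| One-sided 5%, 90% | 8.56 | 105.2, so 106 |
| Printed z values 1.96 and 1.28 (two-sided 5%, 90%) | 10.50 | 129.0 (130 with unrounded z) |

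None gives 120. The K needed is 120 × 4 / (2 × 24.58) = 9.76, which corresponds to none of these settings.

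**A route that does give 120.** Replace the averaged variance by 5.53² = 30.58 and use two-sided 5% with 80% power: N = 2 × 7.849 × 30.58 / 4 = 120.0. This agrees with the first-stated beta of 0.2 but not with the written variance rule, beta = 0.1 or 6.2. Halving alpha for two endpoints, at 80% power with the averaged variance, gives 117. That is near 120 but not equal to it, and the section states no such adjustment.

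**Loss allowance.** 120 × 1.2 = 144. Losing 20% leaves 144 × 0.8 = 115.2. To keep 120 evaluable, 120 / 0.8 = 150 per group are needed.

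**Power for a 2.0 mmHg msDBP difference, two-sided 5%.** Power ≈ Φ(2.0 / (SD × √(2/n)) − 1.96):

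| n per group | Averaged variance (SD 4.958) | SD 5.53 in both groups |
|---|---|---|
| 115 | Φ(3.059 − 1.96) = 86.4% | Φ(2.742 − 1.96) = 78.3% |
| 120 | Φ(3.125 − 1.96) = 87.8% | Φ(2.801 − 1.96) = 80.0% |
| 144 | Φ(3.423 − 1.96) = 92.8% | Φ(3.069 − 1.96) = 86.6% |

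The t test gives slightly less: 86.1%, 87.5% and 92.7% for the averaged variance, and 78.0% for SD 5.53 at 115.

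**Labels.** Values of 8.3 and 6.3 mmHg cannot be diastolic pressures after treatment; they make sense only as reductions. The test group carries the symbol πc and the control group πt. The swap does not affect N, because the difference is squared.

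**The case against.** A reader might infer from the contradictions that the trial has neither of the two stated powers, or is underpowered. The document does not support that. On the protocol's own averaged variance, 97 per group is enough for 80% power, so 115 evaluable exceeds it and falls about 4 points short of 90%.

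The loss step also has little effect. It costs about 5 patients per arm, or 1.4 percentage points of power (87.8% to 86.4%), and the section does not expressly promise 120 evaluable. Moreover, the intention-to-treat population includes everyone randomised, and missing values are filled by LOCF (Analysis population; section {20c}). All 144 per arm would then be analysed, for a nominal power of about 93%. That stands as arithmetic, but only if the assumed difference and SD survive the carrying forward of earlier values.

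It is equally tempting to say that no calculation gives 120. SD 5.53 alone at two-sided 5% and 80% power does. The document does not say that this is where the figure came from, so it remains an inference. It is nevertheless a reason not to delete beta = 0.2 and present 86% as the one true power: if 5.53 was meant as a cautious SD for both arms, 80% was the target and 115 per arm gives about 78%.

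None of this removes the contradiction in the printed text. The route through SD 5.53 conflicts with three of its statements.

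**Conclusion.** The section is wrong as written. Beta has two values, 6.2 is not the squared sum of the z values beside it, and 120 does not follow from the stated formula and variance under any of the error-rate settings above. The 20% allowance leaves about 115 evaluable per group, 5 short of the stated need.

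The consequence is limited. On the averaged variance, power for msDBP is about 86% with 115 evaluable, and nominally about 93% if all 144 are analysed and the assumptions hold. Only if SD 5.53 applies to both groups does power at 115 drop below 80%, to about 78%. These figures assume a true 2.0 mmHg difference and the stated SDs, which come from an earlier study not available here. They concern msDBP only, because the section gives no inputs for msSBP. The defect is an unreliable planning statement, not a demonstrated shortage of patients.

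**What to change.** Keep 288 and rewrite Sample size {14}:

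- State one two-sided alpha of 0.05, one beta, and the SD actually used (the averaged variance, or 5.53 in both groups). The sponsor should say which settings produced 120.
- Replace 6.2 and 120 with values that follow from those choices.
- State that 144 per arm leaves about 115 evaluable after 20% loss, and give the resulting msDBP power: about 86% with the averaged variance, about 78% with SD 5.53.
- After checking the source study, label 8.3 and 6.3 mmHg as DBP reductions, and correct the test and control symbols.

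The cost is wording only: no extra patients and no change to the analysis. The price is a stated power that may be less favourable than 90%.

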#### Recruitment {15}

Researchers and attending physicians will select potential eligible patients based on the inclusion criteria. Patients will be informed in detail about the purpose of the study, procedures, possible side effects, and the benefits of the study, Val/Aml, and TJT. All patients who volunteer to participate are required to sign written informed consent prior to randomization (Additional file 4).

### Assignment of interventions: allocation

#### Sequence generation {16a}

The patients will be randomly divided into two groups by statisticians independent of the intervention and evaluation procedures in clinical trials. The ratio between the treatment group and control group is 1:1. Using the stratified grouping random method, the subcenter will be taken as the stratification factor.

#### Concealment mechanism {16b}

Each participant’s assignment code will be blinded and placed in a sealed opaque envelope. Each envelope will be opened by the researchers to assign the registered participants to a treatment group and control group. In each group, the placebo has identical appearance and smell as TJT.

#### Implementation {16c}

According to the number of patients undertaken by each research center, the statistical software (SAS, version 9.2) will be used to generate a random serial number consistent with the sample size and its corresponding group, i.e., the blind bottom, the random sequence number as the drug number of the study, and remaining blind until the end of the study.

### Assignment of interventions: blinding

#### Who will be blinded {17a}

The following research team members are blinded to the care of the subjects: the clinical investigators, the research staff, and attending physicians.

#### Procedure for unblinding if needed {17b}

The researcher can open the blinding code only when the subject has serious adverse events or other special or emergency events, which necessitates knowing the specific grouping of the subjects before treatment. Researchers should contact the ethics committee to report the reasons for unblinding and record the date of unblinding, treatment, and final results in the CRF form. The subjects should discontinue the study after unblinding. The main investigator will decide whether the research protocol needs to be revised according to safety data after unblinding.

### Data collection and management

#### Plans for assessment and collection of outcomes {18a}

After random allocation, subjects will be followed up for 4 weeks by the researchers and attending physicians at each subcenter. Onsite follow-up tests will be conducted at 2 and 4 weeks, and telephone follow-up will be conducted on day 3 and week 3. The data in CRF come from original documents, such as original medical records and physical and chemical examination reports, and shall be consistent with the original documents. The researchers are responsible for the timely, correct, legible, and complete recording of the data in the CRF and confirm recording by signature. All items in CRF shall be filled in without blank or missing items.

#### Plans to promote participant retention and complete follow-up {18b}

The following are the plans to promote participant retention and complete follow-up:
The researchers will explain the study protocol to the subjects to make them fully understand and cooperate with the test.The researchers will follow up regularly to remind subjects to take medicine on time.The subcenter is equipped with a special clinic for clinical research subjects to reduce their waiting time and create a good medical environment.A diary card will be made, including medication records and precautions during the study.Medical services: the researcher will provide health education to the subjects, including health education knowledge related to hypertension.

#### Data management {19}

To ensure the accuracy of the data, two data managers will independently perform double entry and proofreading. The data management center will be informed of any questions or unexpected situations in the CRF table. The inspector is responsible for monitoring whether the center is compliant with relevant regulations, GCPs, and test schemes to conduct this study. The inspector will cross-check the contents in CRF with the original documents to ensure the consistency of data in CRF with the original data. Data locking will be performed by the data manager at the end of the study. Researchers will not be able to modify the data later, and the Center for Evidence-Based Medicine will be responsible for verifying the data.

#### Confidentiality {27}

The researcher will keep the personal information of all registered subjects safely to protect confidentiality before, during, and after the test.

#### Plans for collection, laboratory evaluation, and storage of biological specimens for genetic or molecular analysis in this trial/future use {33}

No biological specimens are collected in this trial.

## Statistical methods

### Statistical methods for primary and secondary outcomes {20a}

#### Analysis population

The analysis population includes an intention-to-treat (ITT) analysis population and a per-protocol (PP) analysis population. The ITT analysis includes the subjects who express intention to receive treatment, sign informed consent, and are randomized. The PP analysis includes the subjects who complete the trial according to the study protocol.

#### Principles and methods of statistical analysis

All analyses will be conducted with SPSS version 26.0 (IBM SPSS Inc., Armonk, NY, USA) or SAS version 9.4 (SAS Institute, Inc., Cary, NC, USA). The data analysis, data entry, and data management of each research center will be conducted in the Evidence-based Medicine Research Center of Shandong University of Traditional Chinese Medicine. Bilateral tests will be used for all statistical tests, with *P* < 0.05 being considered statistically significant (unless otherwise specified). The 95% confidence interval will be calculated. The quantitative index will include the calculation of the mean, standard deviation, median, minimum, and maximum. The classification index is described by the number of cases and percentages of each category. The two study groups will be compared using an independent two-sample Student’s *t* test. For categorical variables, a *χ*^2^ test will be used when appropriate. A Wilcoxon paired signed-rank test will be used for within-group comparisons.

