### Objectives {7}

The aims of our study were to evaluate the clinical efficacy and safety of TJT combined with Val/Aml SPC in the treatment of essential hypertension (stage 2) with hyperactivity of liver yang and to observe whether Val/Aml combined with TJT can further promote the early achievement of BP and improve clinical symptoms and patient compliance in patients with stage 2 hypertension compared with Val/Aml combined with placebo.

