## Methods: participants, interventions, and outcomes

### Study setting {9}

The trial will be conducted in seven centers in Shandong Province, China, and all these hospitals and their ethics approvals are shown in Additional file 2. A total of 288 participants will be recruited. All the patients will provide written informed consent before participating in this study; recruited patients will be randomly divided into a treatment group (treated with Val/Aml and TJT) or a control group (treated with Val/Aml and placebo) in a 1:1 ratio. After the consent of participants is obtained, a trial will be conducted, including a run-in period of 2 weeks and a treatment period of 4 weeks. The onsite follow-up test of the research center will be conducted at 2 and 4 weeks after random grouping. In addition, telephone follow-up will be conducted on day 3 and week 3.

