#### Inclusion criteria

The following are the inclusion criteria:
Age ≥ 18 years and ≤ 65 years, male or femaleAt the same time, conforming to the diagnostic criteria for stage 2 hypertension [21] and the TCM syndrome differentiation criteria for liver-yang hyperactivity syndrome [22]For patients with primary stage 2 hypertension diagnosed according to established guidelines [21], BP that satisfies any one of the following three criteria:
Patients who have SBP 160–179 mmHg and/or diastolic BP (DBP) 100–109 mmHg, without prior use of any antihypertensive drugsPatients who have been clearly diagnosed with essential hypertension and whose BP is not up to standard after 3 months of improved lifestyle or other forms of nondrug therapy are maintained at 160–179/100–109 mmHgPatients who have been clearly diagnosed with essential hypertension and whose BP is still not up to the standard BP after 3 months of improved lifestyle or other forms of nondrug therapy and oral antihypertensive drugs maintain at 160–179/100–109 mmHgPatients must have had a definite diagnosis of hypertension for more than 3 monthsPatients will be informed about the trial and should voluntarily sign a consent form.

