#### Secondary outcomes

The following are the secondary outcomes:
BP control rate at week 4 (defined as msSBP/msDBP < 140/90 mmHg).To evaluate the improvement of symptoms, the TCM syndrome scoring scale [22] will be used for evaluation (Additional file 3). To determine the degree of symptom improvement, we will refer to the Guiding Principles for Clinical Research on New Chinese Medicines [23]. Efficacy index = [(points before treatment − points after treatment)/points before treatment] × 100%. Significant effect: efficacy index ≥ 70%. Effectiveness: efficacy index ≥ 30%. Invalid: efficacy index < 30%.Other results include blood lipids, blood glucose, urinary microalbumin, uric acid, homocysteine, and hypersensitive C-reactive protein. It should be noted that no biological samples will be collected in our study.In addition, patient compliance will be assessed by counting the number of unused tablets returned at the scheduled visit. Table 1 shows the timing for all outcome measures in the study.

**Table 1 Tab1:** Outcome measures

Domain	Measurement	Time (days)

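### The week-4 BP control rate is to be compared by an unadjusted chi-square that leaves out day-0 blood pressure and the stratifying subcenter: a modest loss of efficiency, not an error

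*Protocol article*

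**What the plan says.** Under Principles and methods of statistical analysis, the article assigns Student's t test to between-group comparisons, the Wilcoxon signed-rank test to within-group changes, and for the rest: "For categorical variables, a *χ*^2^ test will be used when appropriate". Testing is two-sided: "Bilateral tests will be used for all statistical tests".

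The outcome concerned stands under Secondary outcomes: "BP control rate at week 4 (defined as msSBP/msDBP < 140/90 mmHg". It bears on the question in Objectives {7} of whether the combination "can further promote the early achievement of BP".

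Two pieces of information are available by design. Table 1 schedules msSBP and msDBP on day 0. Sequence generation {16a} says that "the subcenter will be taken as the stratification factor", and Study setting {9} gives the number: "The trial will be conducted in seven centers in Shandong Province, China".

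No section brings day-0 pressure or subcenter into an analysis. Section {20b} only says that subgroups will be considered, and {20c} covers only the analysis principles and LOCF.

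**The concern.** The outcome is a fixed cut-off, so a patient's chance of meeting it depends partly on how far above 140/90 that patient starts. Entry allows a spread: "Patients who have SBP 160–179 mmHg and/or diastolic BP (DBP) 100–109 mmHg". Under the and/or wording, a patient may qualify on one pressure while the other lies below the stage 2 range.

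A crude chi-square treats all patients in an arm as exchangeable. Variation that day-0 pressure could explain stays in the error term, and the standard error ignores the balance that stratification by subcenter provides. Adjusting the t test of mean BP change would not help here, because the P value and interval for the control rate would remain crude. At stake is some precision on a secondary outcome, obtainable from data already collected.

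**Working it through.** **1. What the plan quantifies.** Sample size {14} gives 120 per group for mean DBP; no rate or power is given for the control rate, so there is no stated figure to reproduce for this outcome. (With δ² = (5.53² + 4.31²)/2 = 24.58 and a difference of 2.0, the printed formula gives 2 × 6.2 × 24.58/4 = 76, or 129 with (1.96 + 1.28)². That it does not return 120 is a separate matter.)

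For scale, the crude two-sided power under assumed rates is:
- 50% v 60%: 34% at 120 per arm, 40% at 144.
- 50% v 65%: 65% at 120 per arm, 73% at 144.

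**2. Why entry level can matter.** The only DBP inputs are the test group's 8.3 ± 5.53 and "the control group DBP after treatment (*πt*) can be set as follows: DBP, 6.3 ± 4.31 mmHg". Read as normally distributed falls that are the same at every entry level, P(DBP < 90 | entry b) = 1 − Φ((b − 90 − mean)/SD):

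| Entry DBP | Control | TJT |
|---|---|---|
| 100 | 1 − Φ(3.7/4.31) = 19.5% | 1 − Φ(1.7/5.53) = 37.9% |
| 105 | 1 − Φ(8.7/4.31) = 2.2% | 1 − Φ(6.7/5.53) = 11.3% |
| 109 | 1 − Φ(12.7/4.31) = 0.2% | 1 − Φ(10.7/5.53) = 2.7% |

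This is an upper-end picture. A constant fall means a slope of 1.0 of week-4 on day-0 pressure. The table also ignores SBP and leaves out entrants with DBP below 100. The article prints these inputs as values after treatment; reading them as falls is an assumption.

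**3. Size of the loss, with the slope varied.** Simulation with 7 centres, 1:1 within centre, N = 288, 1,500 runs per row. Assumptions: effects of 5 mmHg SBP and 3 mmHg DBP; control-arm rate about 27-35% and TJT rate about 42-53%. Crude chi-square against a risk difference standardised over day-0 msSBP, day-0 msDBP and centre:

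| Entry spread | Slope | Centre SD (mmHg) | Power, crude → adjusted | Variance ratio |
|---|---|---|---|---|
| Narrow | 0.3 | 0 | 91.1% → 91.2% | 0.991 |
| Narrow | 0.6 | 0 | 86.7% → 88.2% | 0.958 |
| Narrow | 1.0 | 0 | 83.9% → 88.1% | 0.899 |
| Narrow | 1.0 | 4 | 80.3% → 85.7% | 0.921 |
| Wide | 0.3 | 0 | 90.1% → 90.3% | 0.989 |
| Wide | 0.6 | 4 | 82.1% → 85.1% | 0.965 |
| Wide | 1.0 | 4 | 75.7% → 80.9% | 0.935 |

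At N = 240 the gains were 0.9 to 5.7 points. Stratifying by centre alone added about nothing without centre variation and 1-3 points with it.

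A second set (120 per arm, residual SDs 10 and 6 mmHg, centre SD 0 or 3) gave:
- Both pressures in range, slope 0.5: variance ratio 0.99-1.00, power 89-91% → 91-92%.
- And/or entry, slope 1.0: variance ratio 0.85-0.86, power 77-79% → 86%. This is the source of the upper limits of 15% and 9 points.

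**4. Type I error.** In the first set (slope 0.6, 5,000 runs, Monte Carlo SE √(0.05 × 0.95/5000) = 0.3 points), the crude test rejected 4.1-4.3% and the standardised difference 4.8-5.3% under the null. In the second set the figures were 4.4-5.0% and 4.5-5.9%. Part of each power gain is therefore a difference in size.

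**5. Few events.** Two further checks used 120 per arm and a standard error without small-sample correction.
- Control rate about 19% (0.19 × 240 ≈ 46 pooled events under the null): null error of the adjusted test 5.4-6.5%. Gains after matching size were 2.6 points at slope 1.0, 1.1 at 0.6 and none at 0.3.
- DBP falls near the plan's inputs, control rate 2-3% (about 5-7 pooled events): null error 7.5-8%. The apparent gain vanished or reversed after matching size.

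**The case against.** The strongest reply is that nothing here is wrong. The comparison is randomised, the chi-square holds its error rate, and the outcome is secondary with no power claimed. Chance baseline imbalance is not bias, and the crude standard error allows for it. All of this stands and limits the point to efficiency.

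A second reply is that covariates for secondary outcomes are commonly left to an SAP, which is not shown. That answers a complaint about a missing detail. Here the article names the test, and its qualifier about appropriateness most naturally leaves room for an exact test; it does not promise adjustment.

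A third reply is that the gain may be negligible. This also stands in part. Patients selected by an entry band will show some regression to the mean, so a slope below 1.0 is plausible. If few reach control, a model with nine terms (arm, two pressures, six centre contrasts) may do worse than the chi-square.

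Two stronger readings are tempting. From the DBP figures a reader might infer that a substantial loss is certain; that depends on the constant-fall assumption, which the documents do not make. A reader might also infer that the control rate, and not the mean change, answers the trial's question. Objectives {7} also names clinical efficacy and safety, and Primary outcomes makes the mean BP changes primary.

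**Conclusion.** The point holds as a modest, inexpensive improvement to a stated method. The named analysis of the control rate leaves out two sources of precision that the design provides. The documents give no expected control rates, no relation between day-0 and week-4 pressure and no centre variation, so the size rests on assumptions.

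With slopes of 0.3-1.0 and centre SDs of 0-4 mmHg across the runs, the variance of the risk difference falls by about 0-10%, up to about 15% with wide and/or entry. A 10% fall is worth 1/0.90 = 1.11, or 11% more patients; 15% is worth 1/0.85 = 1.18. Power rises by about 0-9 points, near zero when day-0 pressure predicts weakly, and part of the rise comes from the slightly different null rejection rates of the two tests. The documents do not support a claim of bias or of inflated type I error in the chi-square.

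**What to change.** In Principles and methods of statistical analysis, name the main analysis of the week-4 BP control rate: a logistic model with arm, day-0 msSBP, day-0 msDBP and subcenter, reported as the standardised (marginal) difference in control rate with a 95% CI, using a small-sample-corrected standard error. This targets the same quantity as the crude difference, which a conditional odds ratio would not. Keep the chi-square as a supporting analysis.

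Prespecify one fallback with a numerical trigger on the pooled count of patients reaching control, read while blinded. An example is a centre-stratified Mantel-Haenszel risk difference when that count is below 9k, with k events for each of the nine terms and k written into the plan. The 46 pooled events in the 19% check correspond to k of about 5 (46/9 = 5.1) and already showed a mildly liberal test without the small-sample correction. The fallback gives up the day-0 pressures, and the plan should say so.

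The cost is a few sentences and slightly more analysis work, with no new data, visits or patients. The downside is little or no gain if few patients reach control. The text should be fixed before unblinding so that the choice between crude and adjusted results is not made on the data.
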